## Abstract

**Background:**

In anterior cervical spine surgery a retractor is obligatory to approach the spine. Previous studies showed an increase of endotracheal tube cuff pressure after placement of a retractor. It is known that high endotracheal tube cuff pressure increases the incidence of postoperative dysphagia, hoarseness, and sore throat. However, until now no evidence supports the fact whether adjusting the endotracheal tube cuff pressure during anterior cervical spine surgery will prevent this comorbidity. We present the design of a randomized controlled trial to determine whether adjusting endotracheal tube cuff pressure after placement of a retractor during anterior cervical spine surgery will prevent postoperative dysphagia.

**Methods/design:**

177 patients (aged 18–90 years) scheduled for anterior cervical spine surgery on 1 or more levels will be included. After intubation, endotracheal tube cuff pressure is manually inflated to 20 mm Hg in all patients. Patients will be randomized into two groups. In the control group endotracheal tube cuff pressure is not adjusted after retractor placement. In the intervention group endotracheal tube cuff pressure after retractor placement is maintained at 20 mm Hg and air is withdrawn when cuff pressure exceeds 20 mm Hg. Endotracheal tube cuff pressure is measured after intubation, before and after placement and removal of the retractor. Again air is inflated if cuff pressure sets below 20 mmHg after removal of the retractor. The primary outcome measure is postoperative dysphagia. Other outcome measures are postoperative hoarseness, postoperative sore throat, degree of dysphagia, length of hospital stay, and pneumonia. The study is a single centre double blind randomized trial in which patients and research nurses will be kept blinded for the allocated treatment during the follow-up period of 2 months.

**Discussion:**

Postoperative dysphagia occurs frequently after anterior cervical spine surgery. This may be related to high endotracheal tube cuff pressure. Whether adaptation and maintaining the pressure after placement of the retractor will decrease the incidence of dysphagia, has to be determined by this trial.

**Trial registration:**

Netherlands Trial Register (NTR) 3542: http://www.trialregister.nl.

## Background

The surgical procedure in patients undergoing anterior cervical spine surgery can only be performed by placement of a retractor system in order to expose the anterior cervical spine. This retractor is placed between the carotic sheath laterally, and the trachea and esophagus medially. Previous studies showed that after positioning and opening the retractor, the endotracheal tube (ETT) cuff pressure increases significantly [1,2]. Structures trapped between the retractor and the endotracheal tube cuff, like the recurrent laryngeal nerve, may be compromised. In patients who were treated with anterior cervical discectomy and fusion, the incidence of recurrent laryngeal nerve injury is about 2%, irrespective of the side of approach [3]. Consequently, dysphagia, hoarseness, and sore throat may occur. These complications occur in other types of surgery as well and may be the result of endotracheal intubation or placement of a laryngeal mask. The overall incidence of postoperative dysphagia after general anesthesia varies from 16 to 60%, hoarseness 21 to 51%, and sore throat from 21 to 74% [1,4-8]. Suggested mechanisms are neuropraxia of the recurrent laryngeal nerve, mucosal injury, postoperative hematoma or edema.

Previous studies have shown that maintaining ETT cuff pressure between 15 and 25 mm Hg can reduce endotracheal intubation-related complications in patients undergoing general anesthesia [9,10]. With regards to anterior cervical spine surgery, lowering the ETT cuff pressure after placement of the retractor may influence postoperative dysphagia, sore throat, and hoarseness. However, a randomized controlled trial showed that pressure adjustment did not reduce the incidence of vocal cord immobility [11]. A small study from 2002 analysed patients undergoing anterior cervical spine surgery and data suggested a lower incidence of sore throat in patients with lower cuff pressures, while a recently performed observational study showed less recurrent laryngeal nerve palsy in patients with reduction of ETT cuff pressure [5,12]. However, until now, adjusting ETT cuff pressure after placement of surgical retractor is not generally performed.

We will evaluate whether ETT cuff pressure adjustment after retractor placement has any influence on postoperative dysphagia, sore throat, and hoarseness. The results of this study may lead to standard adjustment of ETT cuff pressure in all patients undergoing anterior cervical spine surgery.

## Methods/design

We designed a single center, observer and patient blinded randomized controlled trial to investigate whether adjustment of ETT cuff pressure in anterior cervical spine surgery will lead to reduction of postoperative dysphagia, hoarseness and sore throat. The follow-up period is 2 months. The protocol is approved by the medical ethics committee Zuidwest Holland, The Netherlands (number NL35829.098.11). The study will be performed in accordance with the guidelines for good clinical practice.

### Patients

All patients between 18 and 90 years of age requiring primary anterior cervical spine surgery are eligible for this trial. Additional inclusion and exclusion criteria are listed in Table 1. During the patient’s visit to the preoperative outpatient clinic, the anesthesiologist decides whether the patient is eligible for this trial, conform the selection criteria. The study will be explained and, in case of a positive reaction, patients will receive written information. A research nurse will contact the patient a few days after the visit to the outpatient clinic. Informed consent will be obtained just prior to the operation.

**Table 1 T1:** Selection criteria for trial eligibility

	
**Inclusion criteria**	
	● Age 18-90 years
	● Primary anterior cervical spine surgery on 1 or more levels
	● Informed consent
**Exclusion criteria**	
	● Pre-operative dysphagia, hoarseness or sore throat
	● Pre-operative recurrent laryngeal nerve palsy
	● Previous anterior cervical spine surgery
	● Inadequate Dutch language
	● Planned fiberoptic intubation or rapid sequence induction
	● Peroperative use of N_2_O
	● Mentally disabled patients

### Randomization procedure

Subjects will be screened for inclusion into the study and eligible subjects will be randomized to either the intervention or the control group, according to a pre-determined randomization schedule. This randomization was done, using an online randomization program (http://www.randomization.com), using the method of 4 randomly permuted blocks.

In the operating room, after induction of general anesthesia, the anesthesiologist will open an envelope and the allocated treatment will be performed. Patients and research nurses will be kept blinded for the allocated treatment during the follow-up of 2 months.

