### Data analysis

All patients will be randomized in a 1:1 ratio to receive either standard care or adapted cuff pressure. To investigate the association between the presence and severity of dysphagia and cuff pressure, we will compare the two groups by means of chi-square statistics or if necessary with ANOVA. In addition we will use multivariate logistic regression analysis to adjust for potential confounding. A p-value of less than 0.05 will be considered significant. SPSS (version 16.0 or higher SPSS Inc. Chicago, IL) will be used for calculations. Univariate analysis will be performed to identify factors related to dysphagia and secondary outcomes.

Although the numbers of participants are relatively low, we will perform multivariate analysis to evaluate factors that might modify the effect of cuff pressure on various outcome parameters. These factors are determined before analysis and include gender, smoking, duration of surgery, level of surgery, extent of surgery (1 level versus 2 or more levels), and type of implant.

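### The block scheme is ambiguously worded; if it means constant blocks of 4, up to a third of allocations can be deduced in advance by anyone who tracks them all

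*Protocol article*

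**What the plan says.** All references are to the protocol article.

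- **Randomization procedure.** Patients are allocated "according to a pre-determined randomization schedule", produced with an online program "using the method of 4 randomly permuted blocks". No variation in block size is described.
- **Data analysis.** "All patients will be randomized in a 1:1 ratio to receive either standard care or adapted cuff pressure".
- **Methods/design.** "We designed a single center, observer and patient blinded randomized controlled trial".
- **Patients.** At the preoperative clinic "the anesthesiologist decides whether the patient is eligible for this trial". Later, "Informed consent will be obtained just prior to the operation". The section does not say who obtains consent.
- **Randomization procedure, on concealment.** In the operating room, "after induction of general anesthesia, the anesthesiologist will open an envelope and the allocated treatment will be performed". Blinding is stated for patients and research nurses only.

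**The concern.** Permuted blocks force the arms back into balance at the end of every block. Someone who knows the block size and the allocations already made can therefore deduce some of the next ones, and sealed envelopes do not prevent this. The shorter the constant block, the larger the deducible share.

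Here one professional group at one hospital both judges eligibility and learns allocations as envelopes are opened. Enrolment is complete only when consent is given, shortly before surgery. Some exclusions (planned fiberoptic intubation, planned rapid sequence induction, use of N2O) also turn on anaesthetic choices, and the Intervention section leaves the type of general anaesthesia to the attending anaesthesiologist. If an expected allocation influenced, even unconsciously, whether a borderline patient entered, the arms would differ in baseline risk and the difference would pass into the primary dysphagia comparison.

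Tracking is feasible. The Discussion expects 177 patients from December 2011 to the end of 2013, about 25 months. That is 177/25 ≈ 7 a month, so a block of 4 would fill in roughly two and a half weeks.

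**Working it through.** **The plan's own figures.** The article gives no figure for predictability. It gives the sample size, which is used in step 5. With 40% against 20%, two-sided 5% (sidedness is my assumption), 80% power and pooled variance:

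n = [1.96 × √(2 × 0.30 × 0.70) + 0.842 × √(0.40 × 0.60 + 0.20 × 0.80)]² / 0.20² = (1.270 + 0.532)² / 0.04 ≈ 81.2, so 82 per arm, as stated. Then 164 × 1.08 = 177.1, which matches the stated 177.

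**1. Certain allocations, blocks of 4.** A 1:1 block of 4 has 6 equally likely orders. In 2 of them (AABB, BBAA) the last two places are fixed once the first two are known. In the other 4 only the last place is fixed. Expected certain places per block: (2 × 2 + 4 × 1)/6 = 1.333. Share: 1.333/4 = 33.3%, or 59 of 177. In general, for block size B the share is 1/(B/2 + 1).

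**2. Best guessing, blocks of 4.** The chance of a correct guess at places 1 to 4 is 1/2, 2/3, (1/3 × 1 + 2/3 × 1/2) = 2/3, and 1. The mean is 2.833/4 = 70.8%.

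**3. The other reading, and incomplete knowledge.**

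| Situation | Share certain in advance |
|---|---|
| Blocks of 4, every allocation known | 33.3% (about 59 of 177) |
| Blocks of 4, each allocation seen with probability 1/2 | about 8% |
| Blocks of 4, probability 1/3 | about 4% |
| Blocks of 4, probability 1/5 | about 1% |
| Four blocks of about 44, every allocation known | 1/23 = 4.3% (about 8 of 177) |

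The rows with probabilities come from simulation of 177 patients. They represent a caseload split among 2, 3 or 5 anaesthesiologists who do not share information.

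**4. Varying block sizes.** With sizes drawn at random from 4, 6 and 8, an observer who knows that set of sizes and sees every allocation is certain of about 2% (simulation). With 4 and 6 only, it is about 5%.

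**5. What selection could do, on an assumption.** Suppose staff admit patients whose dysphagia risk is v points higher when they expect control and v points lower when they expect intervention. The false difference is 2v(2 × 0.7083 − 1) = 0.83v. The documents give no value for v; 5 points is purely illustrative. The standard error at 82 per arm and 30% incidence is √(2 × 0.30 × 0.70/82) = 7.16 points.

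- All enrolment affected: 0.83 × 5 = 4.2 points, type I error about 9% instead of 5%.
- One third affected: 1.4 points, type I error about 5.4%.

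Both assume blocks of 4, an observer who knows every earlier allocation, and selection always in the same direction.

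**The case against.** The strongest reply is that predictability is not bias, and that the documents leave several links in the chain unproven.

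- **Who sees what.** A reader might infer that the enrolling anaesthesiologists see every allocation. The article does not say so. It names the role at the clinic and the role in the operating room, without saying that they are the same person or that allocations are shared. This stands, and it is why one third is only a ceiling.
- **When selection could happen.** Eligibility is judged at an earlier clinic visit, when the patient's place in the allocation order is not yet settled. The person named as contacting the patient afterwards is a research nurse, a blinded role. This also stands in large part. Consent just before surgery leaves a later opening, but nothing shows that an unblinded person controls it.
- **The envelope is opened after induction.** This is a real safeguard, since the current patient has already consented. It does not protect against deduction from earlier envelopes.
- **Block size 4 is an inference.** A reader might try to exclude the four-large-blocks reading because 4 × 44 is 176, not 177. That proves nothing: 177 is odd, so no set of even blocks adds up to it, and a list can simply run past the target.
- **List handling.** A reader might infer that nobody independent generated or held the list. An article commonly leaves that to the full protocol, so its absence here is no finding.

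**Conclusion.** The point holds as a cheap improvement to a stated design element, not as evidence of a biased trial. The wording of the block scheme needs correcting because its two readings differ about eightfold in predictability (33% against 4%). If constant blocks of 4 were used, the scheme is more predictable than it need be in a single-centre trial where the role that judges eligibility also learns the allocations.

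The 33% rests on three conditions: block size 4, knowledge of that size, and knowledge of every earlier allocation. With split and unshared knowledge it falls to about 8% or less. A reader might take the type I error of about 9% as an estimate for this trial. It is not one: it needs an invented v of 5 points, full knowledge and selection at every enrolment. Any actual bias is probably small, and the article gives no sign that selection has taken place.

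**What to change.** 1. Correct the sentence in the Randomization procedure so that it says whether blocks of size 4 or four blocks in total were used. If four large blocks were used, this largely settles the matter.
2. If constant blocks of 4 were used, replace all unused envelopes with a list in permuted blocks of randomly varying size (for example 4, 6 and 8). The amended text can say that sizes vary, but the sizes themselves should be kept from the anaesthesiologists until the trial closes. This cuts the certain share for a fully informed observer from 33% to about 2%.

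The cost is one regenerated list, a new set of envelopes for the remaining patients and a short amendment. The arms may end a few patients apart: a last block of 8 cut short can leave a difference of at most 4, against 2 for a block of 4. The loss of power is negligible.

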### Intervention

Patients will be randomized into adjustment of the ETT cuff pressure after retractor placement (intervention group), or into no adjustment of the ETT cuff pressure after retractor placement (control group). The type of general anesthesia is determined by the attending anesthesiologist. Intubation is performed by a skilled laryngoscopist with more than 1 year experience. To minimize baseline dysphagia after conventional intubation with a Macintosh laryngoscope, the Glidescope® is used. Endotracheal tube size is 7.0 mm for women and 8.0 mm for men. After intubation, ETT cuff pressure is manually inflated to 20 mm Hg in all study patients. In the control group, no ETT cuff pressure intervention is performed after placement of the retractor. In the intervention group, the ETT cuff pressure is maintained at 20 mm Hg after placement and after removal of the retractor. Air is withdrawn when cuff pressure exceeds 20 mm Hg. In the absence of a device to measure ETT cuff pressure continuously, cuff pressure is measured at several time points: after intubation, before and after placement and removal of the retractor from the start of induction to the end of anesthesia by use of a manometer. The mean intraoperative pressure will be calculated from the values measured directly after insertion of the retractor and just before removal of the retractor. In addition, next to standard patient data, time of retraction, duration of operation, level of operation, number of levels operated on, the use of a cage or other implant, the attending neurosurgeon, and the dose of neuromuscular blocking agent are recorded.

### Surgical procedure

All patients will be positioned supine with their neck in neutral position or slightly extended under general anaesthesia. The affected cervical disc level will be verified with fluoroscopy. A small transverse incision will be made on the right side in all patients. The prevertebral space is approached between the carotic sheath laterally, and the trachea and oesophagus medially. The Caspar Cervical Retractor System (CCR) (Braun Aesculap) or the Trimline retractor (Medtronic) are used in all patients. Depending on the pathology of the patients, the following surgical procedures are performed: 1 level anterior cervical disectomy with interbody fusion (ACDF) or disc prosthesis, 2 level ACDF, or corpectomy with placement of expandable cage.

### Baseline data

Baseline assessment includes age, gender, body mass index, medical history and comorbidity, number of levels operated on, duration of operation, duration retractor placement, and use of cervical implants.

### Outcome measures

The primary outcome measure is postoperative dysphagia documented with the Bazaz dysphagia scale (Table 2) [13]. Secondary outcome measures are postoperative hoarseness, sore throat, degree of dysphagia, incidence of pneumonia, and length of hospital stay. Hoarseness will be scored using a clinician-based voice assessment protocol; Grade, Roughness, Breathiness, Asthenia, Strain (GRBAS) and by using a numeric rating scale (NRS) [14]. A sore throat will be recorded using a numeric rating scale (NRS 0–10).

**Table 2 T2:** Bazaz dysphagia scale

**Do you experience difficulty swallowing?**	
None	No episode of swallowing difficulty.
Mild	Experienced only rare episodes of dysphagia and not considered a significant problem.
Moderate	Occasional swallowing difficulty with specific foods (e.g., bread, steak).
Severe	Frequent difficulty swallowing (e.g., with the majority of foods).

### Outcome assessment

We will assess the above described outcome parameters on two separate occasions; 24 hours following the operation, and 2 months after surgery. Patients are questioned about the presence of dysphagia, hoarseness and sore throat by a blinded observer. Both interviews will be recorded on tape using a high quality digital recorder.

### Sample size

The sample size calculation is based on the hypothesis that the incidence of dysphagia in the intervention group is 20% less than in the control group (40%). Assuming a power of 80%, 82 patients have to participate in each arm. Including 8% loss to follow-up, a total of 177 patients need to be included.

### Data analysis

All patients will be randomized in a 1:1 ratio to receive either standard care or adapted cuff pressure. To investigate the association between the presence and severity of dysphagia and cuff pressure, we will compare the two groups by means of chi-square statistics or if necessary with ANOVA. In addition we will use multivariate logistic regression analysis to adjust for potential confounding. A p-value of less than 0.05 will be considered significant. SPSS (version 16.0 or higher SPSS Inc. Chicago, IL) will be used for calculations. Univariate analysis will be performed to identify factors related to dysphagia and secondary outcomes.

Although the numbers of participants are relatively low, we will perform multivariate analysis to evaluate factors that might modify the effect of cuff pressure on various outcome parameters. These factors are determined before analysis and include gender, smoking, duration of surgery, level of surgery, extent of surgery (1 level versus 2 or more levels), and type of implant.

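### The degree of dysphagia, an ordered four-level secondary outcome, is given a chi-square test or, under an undefined condition, ANOVA; one ordinal test should be named instead

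*Protocol article*

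**What the plan says.** Under Outcome measures: "The primary outcome measure is postoperative dysphagia documented with the Bazaz dysphagia scale". Table 2 gives the scale as four ordered grades: none, mild, moderate and severe. Mild, for example, is defined as "Experienced only rare episodes of dysphagia and not considered a significant problem". The same section lists the degree of dysphagia among the secondary outcomes: "Secondary outcome measures are postoperative hoarseness, sore throat, degree of dysphagia, incidence of pneumonia, and length of hospital stay".

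The Data analysis section opens its test sentence with "To investigate the association between the presence and severity of dysphagia and cuff pressure" and continues: "we will compare the two groups by means of chi-square statistics or if necessary with ANOVA". Presence and severity therefore share one sentence and one pair of tests. The section assigns neither test to either outcome, gives no trigger for moving to ANOVA, and names no method for ordered categories.

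The Sample size section rests on the incidence of dysphagia (presence), not on its degree: "Assuming a power of 80%, 82 patients have to participate in each arm".

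**The concern.** The sentence fits presence but not severity, in two respects.

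- **Efficiency.** A general chi-square on a 2x4 table asks whether the two distributions differ in any way. It spends 3 degrees of freedom and ignores that moderate is worse than mild. If cuff-pressure adjustment shifts patients towards lower grades, a test that uses the order needs only 1 degree of freedom. ANOVA uses the order, but treats the grades as equally spaced numbers on a scale where most patients are expected to score none.
- **Open choice.** Because the condition for ANOVA is undefined, the test for severity could be chosen after the results are known. A choice made that way need not hold the 5% level.

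At stake is the power, and possibly the error rate, of the comparison on the degree of dysphagia. The primary comparison is not at stake.

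**Working it through.** **Inputs from the protocol article.** Control incidence 40%, reduction 20%, power 80%, 82 per arm (Sample size); significance at p < 0.05 and 1:1 allocation (Data analysis); four ordered grades (Table 2).

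**Assumed.** The split of dysphagic patients into mild, moderate and severe is not in the document, so five splits were tried. The test is taken as two-sided.

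**Step 1: reproduce the plan's figure (presence).** With p1 = 0.40, p2 = 0.20 and mean 0.30:

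n = [1.960 × √(2 × 0.30 × 0.70) + 0.842 × √(0.40 × 0.60 + 0.20 × 0.80)]² / 0.20² = (1.270 + 0.532)² / 0.04 ≈ 81.2, so 82 per arm.

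Power at 82 is 80.4%. The figure reproduces if the 20% is an absolute difference; a relative reduction (40% versus 32%) would need 564 per arm. The 2x2 chi-square for presence is therefore adequate.

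**Step 2: what 3 degrees of freedom cost.** The noncentrality that gives 80% power on 1 df is (1.960 + 0.842)² ≈ 7.85. The same noncentrality on 3 df gives 64.5% power, a loss of 15.5 points. This needs no assumption about the severity split.

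**Step 3: simulation for severity.** 82 per arm, 100,000 trials per scenario, 40% versus 20% any dysphagia. Two forms of effect were used:

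- *Proportional odds (PO)*, with odds ratio (0.80/0.20) / (0.60/0.40) = 2.67. For example, controls at 60/20/12/8% give a treated arm of 80.0/11.4/5.4/3.2%.
- *Same mix*: fewer dysphagic patients, with the same severity split among them in both arms.

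| Mild/moderate/severe among dysphagic controls | Effect | 2x4 chi-square | ANOVA, scores 0-3 | Wilcoxon |
|---|---|---|---|---|
| 50/30/20 | PO | 66.1% | 77.8% | 82.0% |
| 50/30/20 | same mix | 64.6% | 70.1% | 79.5% |
| equal thirds | PO | 66.2% | 79.0% | 82.0% |
| equal thirds | same mix | 64.5% | 72.1% | 79.1% |
| 60/30/10 | PO | 65.9% | 77.8% | 82.0% |
| 60/30/10 | same mix | 64.7% | 70.5% | 79.2% |
| 40/40/20 | PO | 66.0% | 78.9% | 81.9% |
| 40/40/20 | same mix | 64.8% | 72.0% | 79.3% |
| 70/25/5 | PO | 65.8% | 77.8% | 81.5% |
| 70/25/5 | same mix | 65.3% | 71.8% | 79.9% |

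Loss against Wilcoxon:

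- 2x4 chi-square: 15.7 to 16.1 points under PO, 14.5 to 14.9 with the same mix.
- ANOVA: 3.0 to 4.2 points under PO, 7.0 to 9.4 with the same mix.

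**Step 4: type I error for severity.** Both arms had the same distribution, with 40% or 30% any dysphagia. Alone, the 2x4 chi-square rejects in 3.9-5.0% of trials, ANOVA in 4.9-5.1% and Wilcoxon in 4.9-5.1%. Taking the smaller p-value of chi-square and ANOVA rejects in 7.2-8.2%.

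**The case against.** The case on the other side is substantial, and much of it stands.

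- **Severity is secondary.** The trial is powered on incidence and claims no power for the degree of dysphagia. This stands. A reader might infer that the primary analysis is weakened; Step 1 shows that it is not.
- **The 15-16 points belong to one reading.** Chi-square for presence and ANOVA for severity is a plausible reading, and the loss is then about 3-10 points. If the chi-square family was meant to include a 1-df trend test, most of the loss disappears. Both readings are possible, but the sentence settles on neither.
- **ANOVA is valid here.** At 82 per arm it holds about 5% despite the skewed grades. This stands; the complaint is lost power and an open choice, not invalidity.
- **Inflation is conditional.** Nothing says that the smaller p-value will be reported. This stands, so the 7-8% is what the wording permits, not what will happen.
- **The detail could sit in an analysis plan.** This does not stand. The article states a method for severity, and a plan that follows it inherits the problem.

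Three stronger readings are also tempting and are not supported:

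- A reader might infer that the same two tests are laid down for length of stay and the 0-10 ratings. The sentence covers dysphagia only, and the article names no group-comparison test for those outcomes. That silence is not an error.
- A reader might put the type I error near 9-10% by adding the 2x2 test to the other two (8.7-9.8% in the same simulations). That mixes multiplicity across two outcomes with the choice of test for one.
- A reader might state flatly that expected counts in the severe cells fall below 5. With 8% severe in controls and 3.2% in the treated arm, the expected count per arm is 82 × (0.080 + 0.032) / 2 ≈ 4.6. With 13.3% and 5.5% it is 82 × (0.133 + 0.055) / 2 ≈ 7.7. The document gives no severe rate.

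**Conclusion.** The point holds for the secondary outcome, degree of dysphagia, and only there. The stated method is poorly matched to an ordered scale, and the choice between its two tests is left open.

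The size depends on how the sentence is read: about 15-16 points of power lost if severity goes to a general 2x4 chi-square, and about 3-10 if it goes to ANOVA. The type I error could be about 7-8% if the test is picked by its p-value, and is about 5% if fixed beforehand.

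The power figures assume 82 evaluable patients per arm, 40% versus 20% any dysphagia, and severity splits that the document does not give. Over the five splits and two forms of effect the chi-square loss hardly moves, because it comes from the extra degrees of freedom; the ANOVA loss is more sensitive to the form of effect.

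**What to change.** Replace the shared sentence with one test per outcome:

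- **Presence of dysphagia (primary):** Pearson chi-square on the 2x2 table.
- **Degree of dysphagia (secondary):** a single pre-specified Wilcoxon-Mann-Whitney test on the four grades, with a proportional-odds common odds ratio and its 95% CI as the effect estimate.
- Delete the ANOVA alternative for this outcome.

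This costs wording only: no more patients, visits or data, and standard procedures. There is one small downside. The common odds ratio rests on proportional odds, so the plan should include a check of that assumption. The error rate of the Wilcoxon test does not depend on it.
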